## Abstract

Young people with physical disability experience challenges to being physically active. To attain the health benefits of physical activity (PA) and sustain engagement, it is essential that participation is meaningful and enjoyable. This study aims to describe current participation in PA by adolescents with physical disability in Ireland, and to establish consensus on their priorities for enhancing physical activity participation. A parallel convergent mixed methods study will be undertaken, comprising a national cross-sectional quantitative assessment of PA participation (“Participation Snapshot”) and Delphi consensus study (“Delphi”). Adolescents (n=100) aged 13–17 years with a physical disability will be invited to take part. The Participation Snapshot primary outcome is the Children’s Assessment of Participation and Enjoyment (CAPE). Contextual factors including underlying medical diagnosis, demographics, mobility (Functional Mobility Scale), hand function (Manual Ability Classification System) and health related quality of life (Child Health Utility 9D) will also be collected. The Delphi will comprise two to four survey rounds, until consensus is reached. Round 1 consists of a bespoke survey, designed and piloted with a public and patient involvement (PPI) panel, with open-ended questions and Likert scales inviting contributions from adolescents on their prior experience and ideas to enhance participation. Responses will be analysed using inductive thematic analysis to construct items and themes, which will then be deductively mapped to the “F-words” and the family of Participation-Related Constructs frameworks. These items will be presented back to participants in subsequent rounds for selection and ranking, until consensus is achieved on the “top 10 priorities” for enhancing PA participation. The project team and PPI panel will then co-design dissemination material and identify targets for dissemination to relevant stakeholder or policy groups. The findings will provide a basis for developing interventions aiming to enhance future PA participation for adolescents with physical disability.

## Introduction

The benefits of regular physical activity (PA) are undisputed. Regular PA can positively influence cardiorespiratory fitness, muscular fitness, cardiometabolic health, bone health and cognitive function for children and adolescents (
World Health Organisation, 2020). Children and young people with disability stand to benefit significantly from sustained PA participation, as demonstrated by the following evidence. Engagement in PA, as measured by the self-reported Physical Activity Questionnaire for Adolescents (PAQ-A), was found to predict quality of life and happiness in adolescents with Cerebral Palsy (CP) (
Maher *et al.*, 2016). Evidence from high-quality randomised controlled trials (RCTs) has shown that young people with disability can gain cardiovascular fitness and strength from participation in PA (
Taylor *et al.*, 2013), particularly PA at a moderate-to-vigorous intensity (
Verschuren *et al.*, 2014). This demonstrates high potential to benefit from PA across multiple domains of health (
Smith *et al.*, 2022).

A recent proposed update to Ireland’s National Physical Activity Guidelines recommend all children and young people with disability to engage in moderate to vigorous activity at least 60 minutes every day, and to include muscle strengthening, flexibility and bone-strengthening exercises three times a week (
Murtagh *et al.*, 2024), though it is noted that health benefits can still accrue with lower amounts. This is reflected in the UK Chief Medical Officer’s guidelines, specific to children and young people with physical disability, which recommend 120 to 180 minutes of aerobic physical activity at a moderate-to-vigorous intensity each week, with strength and balance activities on at least three days per week (
Smith *et al.*, 2022). Despite the guidance and potential benefit, young people with physical disability do not achieve the recommended PA targets and are much less active than their non-disabled peers (
Carlon *et al.*, 2013;
Ryan *et al.*, 2015;
Verschuren *et al.*, 2016). A systematic review, comprising six studies with data from 343 young people with CP and 706 typically-developed peers, found that young people with CP participated in 13–53% less PA and were sedentary for twice the recommended amount (
Carlon *et al.*, 2013). It appears that the COVID-19 pandemic has also impacted PA participation for people with disability: an online public engagement, non-peer reviewed survey of 1,842 disabled people found that just 30% of respondents felt encouraged to return to PA after the pandemic (
Activity Alliance, 2022). The effects of physical inactivity in this population are profound. A recent meta-analysis found higher incidence and prevalence of metabolic, cardiovascular diseases and non-communicable disease, for which physical inactivity is a risk factor, in people with CP (
Ryan *et al.*, 2023). There is an urgent need to address physical inactivity across all populations (
Santos *et al.*, 2023) but particularly in young people with physical disability, who already have lower baseline levels of cardiorespiratory endurance and muscle strength and may be at risk of declining mobility and musculoskeletal complications (
O'Sullivan *et al.*, 2020).

Physical activity can be achieved through incidental physical activity or through planned participation in organised, structured exercise often with other people. Participation, defined in the
International Classification of Functioning, disability and health (ICF) (
World Health Organisation, 2001) as “involvement in a life situation”, is aptly construed as “both a means and an end” (
Imms *et al.*, 2017). The “F-words” conceptualisation of the ICF captures participation under the F-word “friends”, to denote the social interactions from participating with others (
Rosenbaum & Gorter, 2012). Participation could be crucial to sustaining PA. Adolescence is a significant time of change in participation, when adolescents with physical disability shift away from recreational and physical activities towards more social participation (
Imms & Adair, 2017). In a recent systematic review,
McKenzie *et al.* (2021) reported the social and physical environment as strong influences on PA participation in young people and adults with childhood-onset disabilities. They found that social connectedness, social support and the physical environment were fundamental to ‘finding the right balance’, which could tip the balance in favour of being physically active or not. This is an important consideration in informing research into interventions to improve physical activity, as many exercise programmes are not sustained in the medium- to long-term. Understanding how young people participate in PA is crucial to any intervention that aims to enhance and enable sustained PA participation. There is no one-size-fits-all approach to participation (
Shields & Synnot, 2016).

To determine how a participation-based approach could improve physical activity, it is necessary to measure current participation and understand the perspectives of adolescents themselves on the factors that could enhance participation.

## Aim

The aims of this study are:

1. To describe current participation in physical activity by adolescents with physical disability in Ireland;2. To establish consensus among adolescents with physical disability regarding their priorities for enhancing their physical activity participation.

Specific objectives are:

1.To report participation in physical activity over the previous four months by adolescents with physical disability 2.To compare participation between categories of gender, mobility, geography and diagnosis;3.To classify factors that enable or constrain participation in physical activity from free text responses, using the family of participation-related constructs (fPRC) framework4.To describe adolescents’ perceived importance of each factor using data from Likert scales5.To achieve consensus on top 10 priorities for enhancing physical activity participation.

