## Sample size

The target sample size is 100 participants. There is no current national register that captures the total population with the inclusion criteria as outlined, so the sample size was estimated from data from the National Physical and Sensory Disability Database (NPSDD) report 2018 (
NPSDD, 2017) and the Irish national Census in April 2016 (the latest available data at the time of planning the study in September 2021). Extrapolating from Census 2016, 411,519 people living in Ireland would be age 13–17 in 2022 (
CSO, 2016). Considering the known prevalence of some of the included conditions, including CP (1.6 per 1,000 live births) (
McIntyre *et al.*, 2022), SB (1 in 10,000 births in Ireland 2009–2011) (
McDonnell *et al.*, 2015) and BPI (1.7 per 1,000 live births) (
Walsh *et al.*, 2011), we estimate an overall prevalence of physical disability with eligibility for this study of 0.5%, or 2,057 adolescents. This estimate aligns with the NPSDD, of which 10% of its 20,676 registered service users were aged 13–17 years. Taking 2,000 eligible participants as the target population, recruiting 92 participants will give a confidence interval of ±10% for calculation of the Participation Snapshot (
Conroy, 2021). There is no recommended sample size for a Delphi study; a Delphi study on exercise priorities for people with multiple sclerosis (MS) included a comparable sample size of 100 (
Stennett *et al.*, 2018). Therefore, we aim to recruit 100 participants to the Participation Snapshot and Delphi Studies, estimated to be 5% of the target population. 

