## Statistical analysis

The Participation Snapshot will be analysed by descriptive statistics and graphical analysis, in accordance with the objective to describe current participation in PA by young people aged 13-17 across Ireland. Data will be presented disaggregated by gender. As a secondary analysis, we will describe the dependent variables CAPE (primary) and CHU-9D (secondary) by relevant categories of participant characteristics (age, gender, condition, geographical location, mobility
*via* FMS, hand function
*via* MACS).

Delphi Round 1 will be analysed using reflexive thematic analysis, an interpretative approach that facilitates the identification and analysis of patterns or themes in a given data set (
Braun & Clarke, 2021a;
Braun & Clarke, 2021b). The epistemological consideration will be constructionist. As such, the team will consider not just the recurrence, but also the meaning and meaningfulness of the issues arising within the dataset, in determining the themes. An experiential orientation to data interpretation will be adopted to prioritise the respondents’ own accounts of their experience, rather than imposing any expected findings (
Braun & Clarke, 2021a). Analysis will be predominantly inductive, with open coding to represent the meaning as communicated by respondents. Reflexivity notes will be kept at each stage. The software
NVivo 12 (QSR International, Melbourne, Australia) will be used to organise the text in the data set.

A collaborative approach to analysis will be undertaken, with two members of the research team undertaking step 1 (familiarisation) and step 2 (coding) independently. They will then meet to generate initial themes (step 3) through a process of peer debriefing, leading to the creation of a thematic map of themes and subthemes. The “F-words” conceptualisation of the ICF (
Rosenbaum & Gorter, 2012) and the fPRC (
Adair *et al.*, 2018;
Imms *et al.*, 2017). will be used as frameworks for the thematic map. At step 4, themes and the thematic map will be reviewed by the project management team, followed by the creation of a final map and Round 2 of the Delphi survey, which will be piloted by the PPI panellists.

As outlined under subheading “Delphi study”, Round 2, and subsequent rounds, will be analysed using descriptive statistics, specifically, frequency with which an item was positively rated on the sliding or Likert scale, and mean Likert score.

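### Objective 2 is to compare participation between groups, but the analysis plan only describes CAPE by category and gives no between-group difference or its uncertainty

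*Protocol article*

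**What the plan says.** The Aim section sets a descriptive overall aim for this part of the study: "To describe current participation in physical activity by adolescents with physical disability in Ireland". Among the specific objectives, however, the second is comparative: "To compare participation between categories of gender, mobility, geography and diagnosis".

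The Statistical analysis section then fixes the method. "The Participation Snapshot will be analysed by descriptive statistics and graphical analysis", and the section links this to the objective of describing participation. Results will be split by gender. For the other characteristics, "As a secondary analysis, we will describe the dependent variables CAPE (primary) and CHU-9D (secondary) by relevant categories of participant characteristics". The characteristics listed are "age, gender, condition, geographical location, mobility" (by the Functional Mobility Scale) and hand function (by the Manual Ability Classification System). That makes six, where objective 2 names four.

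The Sample size section states "The target sample size is 100 participants". Its basis is "Taking 2,000 eligible participants as the target population", from which "recruiting 92 participants will give a confidence interval of ±10% for calculation of the Participation Snapshot". No between-group difference enters that calculation.

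**The concern.** An objective to compare groups calls for a quantity that expresses the contrast and a measure of its uncertainty. The plan provides category-by-category description, and its only stated precision is for the sample as a whole. A reader of the eventual tables would see different CAPE values in different groups, with no guide to which gaps exceed what sampling variation alone would produce.

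The stake is interpretive. Chance contrasts between modest groups could be reported as findings about gender, mobility, geography or diagnosis. Equally, a real contrast could be passed over because nobody can see how precisely it was measured.

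**Working it through.** **1. The plan's own figure.** Inputs from the Sample size section: target population N = 2,000, half-width d = 10%. Assumed, because the article does not state them: a proportion of 0.5 and a two-sided 95% level.

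- Without finite population correction: n0 = 1.96² × 0.25 / 0.10² = 96.04.
- With correction: n = n0 / (1 + (n0 − 1)/N) = 96.04 / (1 + 95.04/2,000) = 91.7, rounded up to 92.

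The stated 92 is reproduced. At n = 100 the half-width is 9.6% with the correction and 9.8% without. The sample size figure is correct for what it covers, which is one estimate from everyone.

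**2. The same precision within a group.** For a proportion near 50%, without the correction, half-width = 1.96 × √(0.25/n):

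| Group size | 95% half-width |
|---|---|
| 50 | ±13.9 points |
| 33 | ±17.1 points |
| 20 | ±21.9 points |
| 10 | ±31.0 points |

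The ±10% does not carry over to groups.

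**3. A difference between two groups, total n = 100.** The article gives no expected group sizes and no SD for CAPE, so the splits are assumptions and means are expressed in SD units, with equal SD in both groups.

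- Means: half-width = t × √(1/a + 1/b), with t ≈ 1.984 on 98 degrees of freedom.
- Proportions near 50%: half-width = 1.96 × 0.5 × √(1/a + 1/b).

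| Split a/b | √(1/a + 1/b) | Mean difference | Difference in proportions |
|---|---|---|---|
| 50/50 | 0.200 | ±0.397 SD | ±19.6 points |
| 80/20 | 0.250 | ±0.496 SD | ±24.5 points |
| 90/10 | 0.333 | ±0.661 SD | ±32.7 points |

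Using 1.96 in place of t gives ±0.39, ±0.49 and ±0.65 SD, so the choice hardly matters. The finite population correction would narrow the intervals only slightly (9.6% against 9.8% for the whole sample).

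**4. What size of difference could be detected.** With 80% power at two-sided 5%, using normal quantiles, the detectable difference is (1.96 + 0.84) × √(1/a + 1/b). This is 0.56 SD at 50/50, 0.70 SD at 80/20 and 0.93 SD at 90/10. For an assumed true difference of 0.5 SD, power would be about 71%, 52% and 32%. Reaching 80% would need 63 per group.

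**5. Objective against method.** Objective 2 says compare. The analysis section says describe, and names no difference and no interval for one. Where the same section does plan a comparison, it is of respondent characteristics between Delphi rounds, and there it says that the comparison is descriptive. No such statement is made for CAPE by group.

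**The case against.** The strongest reply is that the mismatch is one of verbs. The overall aim is descriptive, the breakdown by category is labelled secondary, and the authors use the idea of comparison in a descriptive sense for the Delphi respondents. Setting CAPE side by side by group would then be the comparison that was meant. Description is also a defensible choice for a sample sized on one estimate. Further, this is a condensed article and a fuller analysis plan may exist, so an unnamed test or model is not an error in itself.

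Much of this stands, and it rules out several stronger inferences that a reader might draw:

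- **That the study cannot say whether any group differs.** Too absolute: observed differences can be described. What is missing is their uncertainty.
- **That the tables will take one characteristic at a time.** This is a natural reading, but the text does not exclude cross-classification.
- **That there will be ten diagnostic cells and 26 county cells.** The ten diagnoses are eligibility bullets, county is a data collection field, and 26 is the number of counties against which one partner's coverage is given. The analysis section speaks only of relevant categories and geographical location.
- **That diagnosis, mobility and geography are confounded.** Overlap is plausible, but the article does not document it, and it describes steps against geographical bias.
- **That a single mutually adjusted model is needed.** Debatable: mobility may lie on the path from diagnosis to participation, so adjusting for it could remove part of the contrast that objective 2 asks about.

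What does not stand is that nothing needs changing. The article states which analysis will be done, and that analysis stops short of a stated objective. An analysis plan that followed it would inherit the gap.

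**Conclusion.** The concern holds in a limited form. The objective promises a comparison, while the stated analysis yields neither an estimated between-group difference nor an interval for one. At n = 100 that uncertainty is too large to leave off the page: from about ±0.40 SD for an even split to about ±0.66 SD for a 90/10 split. These sizes rest on assumed splits, equal SDs and, for percentages, a proportion near 50%. The mismatch between objective and method does not depend on those assumptions. The sample size figure of 92 is not in question. This is a change that should be made to a secondary analysis; it does not undermine the descriptive aim.

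**What to change.** In the Statistical analysis section, add that for gender, mobility, geography and diagnosis, differences in CAPE between a small number of groups fixed in advance will be reported with 95% confidence intervals. Label them exploratory, and give the reason: the sample was not sized for them. Adjusted estimates may be added as a sensitivity analysis if diagnosis and mobility turn out to overlap, but are not required. In the same edit, say how the six characteristics in the analysis section relate to the four in objective 2.

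If only description is intended, reword objective 2 as describing participation by category and draw no between-group conclusions from the tables.

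The cost is a few sentences and a little analysis time, with no extra participants or measurements. The downsides are that grouping loses some detail and that the intervals on display will be wide.

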## Methods and analyses

A cross-sectional convergent mixed methods study will be conducted.
Figure 1 outlines the phases.

**Figure 1. f1:**
[figure not shown]
Participation Snapshot and Delphi Study: Data collection, analysis and integration.

### Participation Snapshot Study

The Participation Snapshot is a cross-sectional study, comprising an online, paper and/or interview led survey, aiming to describe and quantify current participation in PA by adolescents with physical disability in the Republic of Ireland. This will be achieved through quantitative data from standardised scales and Likert scales, supplemented by open-ended questions exploring current participation. The Children’s Assessment of Participation and Enjoyment (CAPE) is the primary outcome measure (
King *et al.*, 2007).

### Delphi Study

The Delphi study is a mixed methods study aiming to determine the Top 10 Priorities from the perspectives of adolescents themselves on the factors that could enhance their participation in PA. The Delphi technique is a well-established approach to achieving consensus between experts in a field, through an iterative process using questionnaires (
Barrett & Heale, 2020;
Stennett *et al.*, 2018). In the Delphi, young people with physical disability will be considered the experts in their lived experience. A minimum of two rounds and maximum of four rounds will be undertaken, until a clear consensus is achieved.

## Public and Patient Involvement (PPI)

A PPI panel, comprising three young people who have a physical disability and three parents/guardians of young people who have a physical disability, works alongside the project team at all stages from inception to dissemination. They helped identify the research question, inputted in the development of the proposal and the methodological approach. They helped develop Round 1 surveys, particularly with regard to language, order and visual appearance, and piloted initial drafts of the online and paper versions. They guided the project team on recruitment strategies and contributed video and photo footage to the promotional material on the
project website.

The PPI panel will similarly input into the design of subsequent Delphi rounds. When consensus is reached on the “Top 10 Priorities”, a focus group will be convened, at which the project team and PPI panel will co-design dissemination materials (including infographics, videos and other media) and identify target audiences with whom to share these outputs.

## Ethics

The study has been approved by the host institution RCSI University of Medicine and Health Sciences Research Ethics Committee (REC202207012) and two lead national disability agencies, the Central Remedial Clinic (REC12118) and Enable Ireland (RA88). As all participants will be under the age of 18 at study commencement, parent/guardian consent will be required, in addition to young person assent. The participant/parent dyad will receive a Parent Information Leaflet, Young Person’s Information Leaflet, and consent form. Study information and materials will also be available on the
study website. Participants who turn 18 during the timeframe of the Delphi study will be re-consented using a Participant Consent Form seeking informed consent, to be completed digitally (for online participants) or written on paper (for paper-based completion).

## Participants and eligibility

Participants will be young people aged 13-17 years at study commencement with a primary diagnosis of physical disability. The definition, from a diagnostic perspective, of primary diagnosis of physical disability has been thoroughly considered in preparing this protocol. The following inclusion criteria will be applied in line with similar diagnostic categories reported by
Anaby *et al.* (2020).

1. A primary diagnosis of one of the following causes of physical disability▪ Cerebral palsy (CP)▪ Spina bifida (SB)▪ Spinal cord injury (SCI) of American Spinal Injuries Association Impairment Scale (AIS) A-D, any neurological level▪ Acquired brain injury caused by stroke or non-invasive cerebral tumour or non-progressive, treated vascular abnormality▪ Traumatic brain injury causing persistent physical disability▪ Skeletal abnormality diagnosed pre- or perinatally, namely achondroplasia or osteogenesis imperfecta▪ Brachial plexus injury (BPI) or obstetric brachial plexus palsy▪ Limb loss▪ Neuromuscular disorder▪ Other disorders as reported by parent/child dyads in the questionnaire2. Able to understand and contribute to questionnaires, either independently or with the support of a family member or therapist. 

